
### Reporting of missing data

The Patient-Reported Outcome Completion and Missing Data (PRO CoMiDa) [50] is a data management tool designed to provide standardised documentation of the completion or reasons for non-completion of patient-reported outcomes assessments by patients in a clinical trial. The form will be completed at each scheduled patient-reported outcomes assessment.

### Data management

All data will be collected and managed using a REDCap [51, 52] database by a blinded research team member. REDCap is a secure web-based application for building and managing online databases and is licensed and supported by the Sydney Local Health District. A digital copy of completed questionnaire forms will also be scanned and uploaded by the study research team onto the Royal Prince Alfred Hospital, Sydney Local Health District secure server. An independent research officer will double-check uploaded records. Hard copy questionnaire forms will be shredded after they have been uploaded. To minimise potential bias arising from missing data at random, multiple imputations will be performed.

### Sample size calculation

To achieve the study’s primary aim, 172 participants will provide 90% power to detect a difference of 25% in complication rates between the intervention and control groups. This difference was considered clinically meaningful by our clinical and consumer panel. These calculations were based upon the overall complication rate being 50% in the control groups, based on our current clinical experience, allowing for up to 5% loss to follow-up and a two-sided alpha of 0.05. The 5% loss to follow-up was estimated from our previous prospective clinical trials [26]. Sample size calculations were conducted using PASS15 software (NCSS LLC).

### Analyses

A comprehensive Statistical Analysis Plan (SAP) and a Health Economic Analysis Plan (HEAP) will be developed by the trial statistician and health economists before database unlocking.

Data analysis will be blinded, following the intention-to-treat principles and guided by a detailed statistical analysis plan. We will restrict the number of analyses to reduce the possibility of Type I errors. Analysis and interpretation (also performed blinded) on the primary and secondary outcomes will be conducted by two independent biostatisticians and checked for accuracy. Demographic and clinical characteristics of the patients in each group will be compared to assess the comparability of the groups. For the primary outcome, a *p*-value of < 0.05 will be considered statistically significant. For the secondary outcomes, a p-value of < 0.01 will be considered significant.

*Primary analysis* (comparison of in-hospital complication rate between groups): Proportions and 95% confidence intervals for in-hospital postoperative complications will be calculated. Differences in this outcome will be compared between intervention and control groups using the chi-square test. *Secondary analysis* (comparison of hospital stay postoperative morbidity and quality of life between groups): Mean and standard deviation (or median [IQR] if applicable) for intensive care and hospital length of stay, postoperative morbidity (including POMS at 5 days postoperative), DAH-30 and quality of life will be calculated. The difference in these outcomes will be compared between the intervention and control groups using an independent sample t-test for normal distributed data and Mann-Whitney U-test for non-normally distributed data. Per-protocol post hoc analyses will be performed to further explore the effects of preoperative exercise and education on the primary and secondary outcomes compared to a control group. Adherence to the preoperative exercise program will be defined as ≥70% attendance of the supervised sessions. To improve the precision of the estimates and to compensate for potential imbalances, estimates will be adjusted for age, sex, type of cancer, preoperative chemo/radiotherapy, and other baseline parameters. Both adjusted and unadjusted estimates will be reported. Linear regression and logistic regression will be used to compare outcomes between groups.

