## Background

For a selected group of patients presenting with advanced primary or recurrent cancers within the pelvis or abdomen, complex and extensive surgery may offer the only chance of long-term survival [1, 2]. Despite the survival benefit, the development of in-hospital postoperative complications after radical surgical resection with the intent of clear surgical margin remains very high [3]. For patients undergoing pelvic exenteration, cytoreductive and advanced upper gastrointestinal cancer surgeries, postoperative complication rates can range from 40 to 70% [4, 5] and comprise debilitating complications, including anastomotic leak, ileus, wound infection, sepsis, severe bleeding and pneumonia [6, 7]. These are major complications which require intensive treatment, prolonging hospital stay, reducing patient’s quality of life [1, 8, 9] and increasing the cost of care [10, 11].

Recent evidence suggests that the patient’s preoperative status largely determines the risk of developing postoperative complications following cancer surgery [12]. Patients presenting a low level of physical fitness during the preoperative period were more likely to develop postoperative complications [13, 14] while higher levels of self-reported physical activity were associated with improved postoperative outcomes [15]. Over the past decade, preoperative exercise has gained popularity, with the intent of strengthening functional capacity before surgery, accelerating the return to the preoperative conditions. To date, several randomised controlled trials (RCTs) have been conducted to investigate the effectiveness of a wide range of preoperative exercise programs in reducing postoperative complications and length of hospital stay in patients undergoing cancer surgery [16].

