### Study sites

This multicentre trial will be performed in three centres in Australia: Royal Prince Alfred Hospital (leading trial site) and the Chris O’Brien Lifehouse (satellite site) in Sydney, and the Peter MacCallum Cancer Centre in Melbourne. These sites are nationally recognised as leading centres for managing patients undergoing major advanced primary or recurrent gastrointestinal cancer surgery in Australia.

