### Randomisation and blinding

Consenting participants will undergo baseline assessment immediately before randomisation to intervention (prehabilitation with a progressive preoperative exercise and education program) or control group (usual care alone). An experienced biostatistician, not involved in patient recruitment or data collection, will create the randomisation sequence a priori using a central secure (computerised) randomisation service (1:1 allocation ratio in random permuted blocks of sizes 4 or 2 stratified by site, to ensure balance in treatment assignment within the study sites) to ensure concealment of treatment allocation and blinding of the treating surgeon, all trial personnel and the statistician. The randomisation schedule (i.e., allocation tables as Microsoft Excel file) will be uploaded by an independent Research Officer (not involved in the trial) into the PRIORITY TRIAL’s Research Electronic Data Capture (REDCap) database. The REDCap randomisation module will randomise participants into the intervention or control group. Due to the nature of the intervention, it is not possible to blind the clinicians delivering the intervention (exercise and education program); however, we will ensure that all patients’ interactions are standardised.

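### Randomisation is stratified by site but the primary chi-square test is not: the test stays valid, is slightly conservative if sites differ in risk, and can be improved at no cost

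*Protocol article*

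**What the plan says.** Under Study sites: "This multicentre trial will be performed in three centres in Australia". Under Randomisation and blinding, allocation follows a "1:1 allocation ratio in random permuted blocks of sizes 4 or 2 stratified by site". Site is the only stratification factor.

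Under Analyses, the primary analysis consists of proportions with 95% confidence intervals and a test: "Differences in this outcome will be compared between intervention and control groups using the chi-square test". No site term appears, and the primary outcome is judged at p < 0.05.

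The same section adds that "estimates will be adjusted for age, sex, type of cancer, preoperative chemo/radiotherapy, and other baseline parameters", that "Both adjusted and unadjusted estimates will be reported", and that "Linear regression and logistic regression will be used to compare outcomes between groups". Neither site nor surgical procedure is named. A detailed statistical analysis plan is to follow before the database is unlocked.

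**The concern.** Small blocks within each site hold the arms nearly equal in size at every site, so a difference in risk between sites can hardly shift the treatment contrast. The chi-square test ignores this. Its pooled variance counts the spread of risk between sites as if it were noise in the comparison. The standard error is then larger than the design warrants, the true type I error falls below the nominal level, and some power is given away.

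The adjusted estimates do not clearly repair this, because the one factor used in the randomisation is not on the named list. At stake is some precision in the primary comparison, which the data already held would recover.

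**Working it through.** **Inputs from the protocol article.** Sample size calculation: 172 randomised, control rate 50%, difference 25 points (so 25% in the intervention arm), 5% loss, two-sided alpha 0.05, 90% power. Study sites: three sites. Randomisation: 1:1 in blocks within site.

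**Assumed inputs.** The article gives no complication rate by site and no site sizes. The main runs assume 54 evaluable patients per site (162 in all) and site control rates from equal to widely spread. The Background says "postoperative complication rates can range from 40 to 70" per cent across types of surgery. That range is borrowed here as a plausible spread between sites; 30/50/70% is a deliberately wider case.

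**Step 1: the plan's own power.** Evaluable: 172 × 0.95 = 163.4, or 81.7 per arm. With mean rate 0.375:

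- Null term: 1.96 × √(2 × 0.375 × 0.625) = 1.342
- Alternative SD: √(0.5 × 0.5 + 0.25 × 0.75) = 0.661
- z = (0.25 × √81.7 − 1.342) / 0.661 = 1.39, so power is 91.7%

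Exact enumeration of the uncorrected chi-square gives 91.5% at 81 per arm and 91.6% at 82. The stated 90% is met.

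**Step 2: how much too wide the standard error is.** Under the null, with rates p at equal-sized sites and mean p̄, the pooled variance p̄(1 − p̄) equals the mean within-site variance plus the between-site variance of p. For 40/50/70%:

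- p̄ = 0.5333, so p̄(1 − p̄) = 0.2489
- Mean within-site variance: (0.24 + 0.25 + 0.21)/3 = 0.2333
- Ratio of standard errors: √(0.2489/0.2333) = 1.033

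The pooled standard error is about 3% too wide. The effective critical value is 1.96 × 1.033 = 2.02, which implies a type I error of about 4.3%.

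**Step 3: simulation.** 100,000 trials per scenario, arms balanced within site, treatment effect a constant odds ratio calibrated to an overall 25-point difference. Each pair is chi-square v site-stratified Cochran-Mantel-Haenszel (CMH).

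| Site control rates | SE ratio | Type I error | Power at 25 points |
|---|---|---|---|
| 50/50/50% | 1.000 | 5.0% v 5.0% | 91.5% v 91.4% |
| 40/50/60% | 1.014 | 4.7% v 4.9% | 91.8% v 92.2% |
| 40/50/70% | 1.033 | 4.1% v 4.8% | 90.9% v 92.3% |
| 30/50/70% | 1.058 | 3.9% v 5.1% | 92.5% v 93.9% |

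Unequal sites (100/30/32 patients, rates 40/55/70%) give 4.2% v 4.7% and 92.5% v 93.3%. Further runs at 40/50/70% gave type I error of 4.2 to 4.5% for the chi-square and 4.9% for CMH, with power of 91.0 to 92.2% v 92.3 to 93.4%.

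**Step 4: procedure.** With six procedure groups spread over 40 to 70%, stratifying the test by procedure moves power from 90.6% to 91.4%. That run held the arms balanced within procedure, which the actual randomisation does not do. It therefore shows only that the gain in precision is small, and says nothing about the chi-square's type I error.

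**The case against.** The strongest reply is that nothing here is broken. The chi-square holds its type I error at or below 5%, so a significant result can be trusted. It keeps its planned power in every scenario tried, and the whole effect depends on site differences the article does not report. All of this stands, and it sets the grade.

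Three stronger readings are tempting, and the document supports none of them:

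- **That the primary inference is wrong and power is lost outright.** The standard error is at most slightly too wide, and only if sites differ. Larger losses do appear at a 20-point effect (75.1% v 77.5% with assumed sites of 80/40/44 and rates 40/50/70%; 78.3% v 82.6% at 30/50/70%), but the trial is designed for 25 points.
- **That the open-ended covariate list compromises the primary result.** The list cannot affect a chi-square test. Choosing covariates after seeing the baseline table is an inference that the text does not state. The analysis is to be blinded and guided by an analysis plan that is not shown, and closing a covariate list is commonly left to that plan.
- **That leaving out procedure is the same fault as leaving out site.** Procedure is not a stratification factor, so its absence costs precision only. Type of cancer partly stands in for it, and the unspecified remainder of the list could include both. The 40 to 70% range assigns no rate to any one procedure or site.

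What survives is that the article fixes a specific primary test, and that test does not use the stratification in the design.

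**Conclusion.** The mismatch is real and its effect is small. The primary test is valid and mildly conservative when sites differ in risk. At assumed site control rates of 40/50/70%, type I error is about 4.1 to 4.5%, the standard error is about 3% too wide, and 1 to 1.5 points of power are lost at the 25-point design effect. With equal site rates nothing is lost.

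Power stays above 90% throughout. This assumes the chi-square is run without a continuity correction; with one, power at 82 per arm is 88.9%, a matter separate from stratification. The sizes also rest on the assumed site rates and site sizes, and on arms balanced within site.

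A reader might infer that the trial's main result would be unreliable. It would not be: any error is in the cautious direction. The grade is optional to should-fix, not must-fix.

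**What to change.** - **Primary analysis:** name one site-stratified analysis, namely a CMH test stratified by site, reported with a Mantel-Haenszel risk difference and 95% confidence interval, also stratified by site. State that its p-value decides at 0.05.
- **Supportive analysis:** keep the unstratified chi-square, labelled as supportive.
- **Secondary adjusted logistic model:** add site and procedure group (sparse procedures pooled) to the covariates already named: age, sex, type of cancer and preoperative chemo/radiotherapy.

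The cost is a few sentences in the analysis plan, before the database is unlocked. Site is already recorded for randomisation and the operation is known for every patient, so no new data, patients or change to the sample size are needed. If sites turn out not to differ, the stratified test performs practically the same as the chi-square (91.4% v 91.5% power), so the change carries no meaningful penalty.

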#### Secondary outcome measures

The secondary outcomes will be:(i)*Intensive care unit and hospital length of stay:* The duration of stay in the intensive care unit and hospital (in days); with the day of the index surgery considered as day 0. This information will be extracted from the hospital’s electronic medical records.(ii)*Quality of life*: measured by the Short Form 36 version 2 (SF-36v2®, Australian English) [35] at baseline (4-8 weeks preoperative), within the week before surgery, discharge day, and 3 months postoperative. The QualityMetric Health Outcomes™ Scoring Software will be used to obtain the final scores of the eight quality of life domains (physical functioning, role physical, bodily pain, general health, vitality, social functioning, role emotional, and mental health) and the two physical and mental summary scores.(iii)*Postoperative morbidity*: Further investigations on postoperative morbidity will be conducted as a secondary outcome measure:*Morbidity on postoperative day five and postoperative day 30*: Morbidity on postoperative day 5 (or the day of discharge if the participant is discharged earlier) will be assessed by the Postoperative Morbidity Survey (POMS) [36] and morbidity on postoperative day 30 will be captured using the postoperative complication definition recommended by the StEP-COMPAQ group [34]. The severity of each complication will be graded using Clavien-Dindo classification [37, 38]. The overall postoperative morbidity will also be expressed using the Comprehensive Complication Index (CCI) [39] which weights patients with multiple complications higher than patients with only a single complication yet of the same highest Clavien-Dindo severity grade.*Days at home within first 30 days after surgery (DAH-30)*: DAH-30 is a composite measure that accounts for the length of stay in the hospital following index surgery (Day 0), readmission to either the index or any other hospital, hospital discharge to a rehabilitation centre/hospital or nursing facility, and early deaths after surgery within a single metric. DAH-30 (number, value between 0 and 30) will be calculated using mortality and hospitalisation data from the date of the index surgery (day 0). For example, if a patient dies on postoperative day three, they will be assigned 0 for DAH-30. If a patient is discharged from the hospital on day six after surgery but is subsequently readmitted for 4 days before their second hospital discharge, the patient will be assigned 20 (=30-6-4) DAH-30. If a patient has complications and spends 16 days in the hospital, then is transferred to a nursing facility for rehabilitation, and spends 24 days there before finally being discharged to their own home, the patient would be assigned 0 (30-16-24 = − 10, set to 0) for DAH-30. If a patient dies within 30 days of surgery, irrespective of whether the patient has spent some time at home, DAH-30 will be scored as zero (0) [40, 41].(iv)*Health resource use (costs) and productivity losses*: Information on patient out-of-pocket and health system resource use (in Australian dollars, AUD), including the cost of the exercise intervention, will be collected (via follow-up questionnaires) from randomisation up to 3 months postoperative [11]. Information about the impact of the intervention and surgery on return to work and leisure activities will be used to inform productivity losses.

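### The stated between-group test for SF-36 uses neither its baseline score nor site, and the plan does not say whether that test or the adjusted regression leads

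*Protocol article*

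**What the plan says.** The Secondary outcome measures section has SF-36 collected "at baseline (4-8 weeks preoperative), within the week before surgery, discharge day, and 3 months postoperative". The Randomisation and blinding section places the baseline assessment immediately before randomisation and stratifies allocation by site.

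The Analyses section then describes two analyses of the secondary outcomes.

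- **Unadjusted.** Means and standard deviations, or medians and interquartile ranges, "for intensive care and hospital length of stay, postoperative morbidity (including POMS at 5 days postoperative), DAH-30 and quality of life will be calculated". The groups are compared "using an independent sample t-test for normal distributed data and Mann-Whitney U-test for non-normally distributed data".
- **Adjusted.** To gain precision and offset imbalances, "estimates will be adjusted for age, sex, type of cancer, preoperative chemo/radiotherapy, and other baseline parameters". "Linear regression and logistic regression will be used to compare outcomes between groups", and "Both adjusted and unadjusted estimates will be reported".

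Neither analysis is named as the main one. Significance for secondary outcomes is set at 0.01.

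Length of stay is defined as "The duration of stay in the intensive care unit and hospital (in days); with the day of the index surgery considered as day 0", with no statement about patients who die in hospital. Days at home to day 30 (DAH-30) does have such a rule; for example, "if a patient dies on postoperative day three, they will be assigned 0 for DAH-30".

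**The concern.** SF-36 is the one listed secondary outcome with a pre-randomisation measurement of itself, and that value is usually a strong candidate predictor of the follow-up score. A two-sample t-test or Mann-Whitney test of follow-up scores ignores it. It also ignores site, which the design took the trouble to balance. The adjusted analysis could repair both omissions, but it names neither variable, and the reader cannot tell whether it outranks the unadjusted test.

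Two things are at stake. The first is precision: the 0.01 threshold already makes a quality-of-life effect harder to show, and the stated test makes no use of information the trial will hold. The second is interpretation: if the adjusted and unadjusted results fall on different sides of 0.01, the protocol does not say which one answers the question.

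**Working it through.** **Inputs from the protocol.** 172 participants, 1:1 allocation, 5% loss, primary rates of 50% against 25%, primary alpha 0.05 two-sided, secondary alpha 0.01.

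**Assumptions.** The 0.01 is two-sided. The correlation r between baseline and follow-up SF-36 is 0.3, 0.5 or 0.6. An illustrative true effect of 0.5 SD is used for power.

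**Step 1: analysable number, checked against the plan's own figure.** 172 × 0.95 / 2 = 81.7, taken as 82 per arm. For the primary outcome, with pooled rate 0.375:

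z = [0.25 × √82 − 1.960 × √(2 × 0.375 × 0.625)] / √(0.25 + 0.1875) = (2.264 − 1.342) / 0.661 = 1.394, so power is 91.8%.

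This agrees with the stated 90% to within two points, so 82 per arm is a fair base. The protocol gives no power figure for secondary outcomes.

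**Step 2: unadjusted SF-36 comparison at 0.01.** Detectable difference at 80% power = (2.576 + 0.842) × √(2/82) = 3.418 × 0.1562 = 0.534 SD.

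**Step 3: baseline-adjusted comparison.** ANCOVA multiplies the residual SD by √(1 − r²), so the detectable difference is 0.534 × √(1 − r²). The gain expressed in patients is 1/(1 − r²). Power at 0.5 SD is Φ[0.5 / (0.1562 × √(1 − r²)) − 2.576].

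| Analysis | √(1 − r²) | Detectable difference | Equivalent patients | Power at 0.5 SD |
|---|---|---|---|---|
| Unadjusted | 1 | 0.53 SD | 1.00 | 73.4% |
| r = 0.3 | 0.954 | 0.51 SD | 1.10 | 78.2% |
| r = 0.5 | 0.866 | 0.46 SD | 1.33 | 86.9% |
| r = 0.6 | 0.800 | 0.43 SD | 1.56 | 92.3% |

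If SF-36 loss at 3 months exceeds 5%, every detectable difference grows by the same factor, and the ratio between the rows is unchanged.

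**Step 4: would change scores do the same job?** The protocol does not say whether follow-up or change scores enter the test. With equal SDs at both visits, a change score has variance 2(1 − r) relative to the follow-up score. The detectable difference is then 0.534 × √1.4 = 0.63 SD at r = 0.3, 0.534 × √1.0 = 0.53 SD at r = 0.5, and 0.534 × √0.8 = 0.48 SD at r = 0.6. In each case this is worse than ANCOVA.

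**Step 5: how much could death matter for length of stay?** A simulation used 82 per arm, lognormal stays (median 14 days, log-SD 0.6) with no true effect, and all deaths in the control arm on days 1 to 7. These are all assumptions. The measure is the probability that an intervention patient has the better stay than a control patient; no effect is 0.50.

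- 2% control deaths: 0.490 if death simply ends the stay, 0.510 if death takes the worst rank.
- 5% control deaths: 0.476 and 0.523.

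The direction changes, but the shift from 0.50 is only about 0.01 to 0.025.

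**The case against.** The strongest reply is that the plan already contains the remedy. Linear regression of follow-up SF-36 on arm and baseline SF-36 is ANCOVA, and the adjustment list ends in an open phrase that can include the baseline score. The stated purposes of that adjustment are precision and balance. This stands against any claim that baseline SF-36 will go unused: a reader might infer that from the t-test sentence, but the paragraph as a whole does not support it. What remains is that the baseline score and site are not named, the list is open, and the adjusted result is not made the main one.

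Nor is the unadjusted test invalid. Over randomisation it is unbiased; the loss is one of precision and of protection against a chance imbalance in this particular sample.

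A reader might also infer that the plan counts an early in-hospital death as a good, short stay. No sentence says so. It is a silence that a statistical analysis plan commonly fills, and DAH-30 already penalises death among the secondary outcomes.

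Finally, choosing the test by distribution might be read as a route to selective testing. The protocol calls for blinded analysis by two independent biostatisticians under a plan written in advance, and for a skewed stay and a bounded DAH-30 the rule already points to Mann-Whitney. That part is mostly a matter of good practice.

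**Conclusion.** The point holds for SF-36. The protocol fixes an unadjusted test that ignores the baseline score and site, sets an adjusted regression with an open covariate list beside it, and ranks neither. Relying on the unadjusted test means a detectable effect of 0.53 SD where 0.43 to 0.51 SD is attainable for correlations of 0.6 down to 0.3, at 82 per arm, two-sided 0.01 and 80% power. The gain is small at r = 0.3 and substantial from 0.5 upwards; the correlation is an assumption throughout.

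This is a worthwhile improvement at no data cost and should be made. It concerns secondary outcomes only and leaves the sample size and primary analysis untouched. The length-of-stay death rule is a minor clarification: its effect depends on mortality, which the protocol does not give, and is likely small.

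**What to change.** In the statistical analysis plan, before database unlocking:

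- **SF-36.** Make ANCOVA, or one mixed model over the two postoperative visits, the main analysis, with the pre-randomisation SF-36 score and site as covariates and 3 months as the reference visit. The score from the week before surgery is measured after randomisation and should not serve as the baseline. Name any further covariates so that the list is closed. Keep the unadjusted test as supportive.
- **Length of stay and DAH-30.** Prespecify a site-stratified rank test (van Elteren) instead of letting the observed distribution choose.
- **In-hospital death.** Add one sentence on how it enters length of stay, for example worst rank, which would agree with the DAH-30 rule.

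The cost is wording only: baseline SF-36 and site are already collected. The one drawback is that length of stay is then tested on ranks rather than as a mean difference; medians and interquartile ranges can still be reported alongside.
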